#### Ongoing support (Group B)

In addition to the programme of specialist MDT rehabilitation, participants randomised to Group B will receive ongoing support for four months from a care assistant trained in Parkinson's, starting at the end of the six week MDT intervention. The care assistants will be part of the MDT and will work under the supervision of the PNS. About one hour per week per patient is allowed for ongoing support, and contact will to be through a mix of home visits and telephone, through which the care assistant will monitor progress in implementation of the agreed care plan and report back to the MDT. If required, MDT members may continue to provide input. Care assistants will be recruited to the project from local health and social care employers and trained using the material developed by the research team [45], and through shadowing MDT members.

#### Usual Care/Control (Group C)

Participants in the control group will continue to receive care as usual (no coordinated MDT care planning or ongoing support). When informed of their group allocation, they will be sent locally relevant and generic information about Parkinson's disease. This is a small enhancement on the service they are likely to be receiving. In order to measure the impact of the interventions, this information will also be given to the participants in Groups A and B. At the end of the trial, people in the control group will be offered an assessment by the MDT, with advice, and the fact sheets provided to groups A and B, but additional services cannot be guaranteed.

Cross contamination between groups will be minimal because patients will be individually recruited to the study, and receive treatments tailored to their specific needs. Moreover, the intervention and research assessments will take place in participants' homes which will be geographically dispersed over the catchment areas of three large district general hospitals.

### Outcome measures

Participants in all groups will be assessed in their homes by a research nurse, according to the schedule used in the day hospital trial, at weeks 6 (after the rehabilitation intervention), 24 (four months after the end rehabilitation, coinciding with the end ongoing support for Group B), and 36 (for final follow up). Validated instruments which reflect the needs of participants (e.g. functional outcomes, quality of life) and service commissioners (e.g. service use), and which have been found sensitive in previous rehabilitation studies undertaken by the research team [10-13] have been selected to measure outcomes (Table 1).

**Table 1 T1:** Trial outcome measures and instruments: baseline, 6, 24 and 36 weeks

Participant	Outcome measure	Instrument
Person with Parkinson's	Parkinson's disability/general activities	Self Assessment Parkinson's Disease Disability Scale [46] (PRIMARY OUTCOME)
	
	Parkinson's specific	Parkinson's Disease Questionnaire [47]
		
		Non Motor Symptom Questionnaire [48]
	
	Mobility	Posture and gait items from the Unified Parkinson's Disease Rating Scale [49]
		
		Timed up and go [50]
	
	Falls	Self report
	
	Speech	Single speech item from the Unified Parkinson's Disease Rating Scale [49]
		
		Abridged Emerson and Enderby Screening Assessment Rating Scale [51]
		
		Frenchay Dysarthria Summary [52]
		
		Speech self report questionnaire [10-12]
	
	Pain	Visual analogue scale [53]
	
	Generic health related quality of life/QALYs	Euro Qol 5D, with utility index for calculation of quality adjusted life years (QALYs) [54]
	
	Self efficacy	Self efficacy scale [55]
	
	Health and social care utilisation	Customised proforma and patient records

Live-in carer	Carer strain	Modified caregiver strain index [56] (PRIMARY OUTCOME)
	
	General health	General health questionnaire - 12 [57]

Both	Activities of daily living	Barthel ADL index [58]
	
	Social activities	Frenchay Activities index [59]
	
	Psychological wellbeing	Hospital Anxiety and Depression Scale [60]
		
		Yale single item depression screening tool [61]
	
	Generic health related quality of life	Short form - 36 Health Survey [62]

The instrument battery was developed and piloted in collaboration with patient and carer representatives. It takes about one hour to complete, and was not been found too onerous. Research nurses will assist patients with completion of questionnaires. Carers will be asked to self complete the questionnaires that apply to them. All questionnaires will be checked for completeness before the research nurse leaves the participant's home. Data will be entered by the research nurse shortly after collection, and any queries referred back to the participant by telephone. A further check on data (completeness and entry) will be undertaken by the research manager when forms are returned to the office by the research nurse, and missing items or other issues will be resolved. Patient and carer outcomes will be analysed separately.

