### Inclusion criteria

People with Parkinson's (any stage of the disease) will be included if they: are 18 years of age or over; have a clinical diagnosis of Parkinson's disease; are living in the community (own home or minimally sheltered accommodation) with their own living areas; live in the county of Surrey (for reasons associated with the funding of the intervention); are able to read and write English in order to complete the self report questionnaires; express a commitment to participate over the duration of the study and provide written consent.

Live-in carers will be included if they: are 18 years of age, or over; are able to read and write English in order to complete the self report questionnaires; express a commitment to participate over the duration of the study and provide written consent.

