### Blinding

The research administrator will not disclose group allocation to the research nurses who undertake assessments, and participants will be asked not to discuss aspects of the trial and treatments with them. However, it is recognised that blinding of the research nurses may be compromised in trials of this nature. As a check on blinding, research nurses will be asked to guess participants' groups at the end of the trial. For data analysis, the group identifiers will not be disclosed to the statistician.

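### Research nurses whose blinding may be lost help patients complete the self-assessed primary outcome, which adds a nurse-mediated route for detection bias that a simple procedure would reduce

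*Protocol article*

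**What the plan says.** All references are to the protocol article.

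- **Instrument.** Table 1 (Outcome measures) names the Self Assessment Parkinson's Disease Disability Scale as the patient primary outcome and the modified caregiver strain index as the carer primary outcome.
- **Completion.** The same section says "Research nurses will assist patients with completion of questionnaires". For carers it says "Carers will be asked to self complete the questionnaires that apply to them". For both, "All questionnaires will be checked for completeness before the research nurse leaves the participant's home", and the nurse then enters the data.
- **Blinding.** "The research administrator will not disclose group allocation to the research nurses who undertake assessments", and participants are asked not to talk to the nurses about the trial or their treatment. The section adds that "it is recognised that blinding of the research nurses may be compromised in trials of this nature". As a check, nurses guess each participant's group at the end of the trial.
- **Who knows the arm.** Under Registration and randomisation, every participant is told the allocated group. Baseline data are collected before randomisation.
- **Eligibility.** Patients are included if they "are able to read and write English in order to complete the self report questionnaires".
- **Week 24 interview.** Under Acceptability of the intervention, feedback interviews with participants in groups A and B take place during the 24 week research assessment. The interviewer is not named.
- **Analysis.** Under Statistical methods, groups are compared on change scores, mainly from baseline to weeks 6, 24 and 36.

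**The concern.** A self-assessment is meant to carry the patient's own judgement. Once another person helps to fill it in, that person's expectations can enter through how an item is explained, which answer is suggested, or how a hesitant reply is recorded. If the helper does not know the arm, this adds noise or a shift common to all groups. If the helper does know it, the shift can differ between groups and be read as a treatment effect.

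The plan combines the two conditions. Help is the stated rule for patients, and the helpers are the assessors whose blinding is acknowledged to be at risk. An hour in the home discussing daily function with a patient who knows the allocation is a natural occasion for it to come out. An interview held only with groups A and B at the week 24 visit could reveal it outright if the same nurse conducts it or is present.

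At stake is how a difference on the patient primary outcome can be interpreted. Patients' own awareness of allocation is an unavoidable limitation here. Influence from the nurse can at least be reduced.

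**Working it through.** **1. How help enters the comparison.** Write a patient's observed change as true change + (h at follow-up − h at baseline), where h is the effect of help on the score. Baseline precedes randomisation, so the mean of h at baseline has no expected difference between arms. The bias in, say, A versus C is therefore the mean of h at follow-up in A minus its mean in C. It is zero if help shifts scores equally in both arms. It is non-zero if help differs in amount or effect by arm, which nurse knowledge of the arm makes possible.

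**2. The two primary outcomes side by side.**

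| Feature | Patient disability | Carer strain |
|---|---|---|
| Respondent knows the arm | Yes (patients told) | Yes (participants told) |
| Nurse helps with completion | Yes, as a rule | No, self-completed |
| Nurse checks form and enters data | Yes | Yes |

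The help step is the only difference. It adds one route to those that both outcomes already have.

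**3. The plan's own sample size, as a base for scale.** Inputs from Sample size calculations: difference 1.25, SD 2.5, two-sided 5%, power 80%.

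- Standardised difference: 1.25/2.5 = 0.5.
- Normal approximation: n = 2 × (1.960 + 0.842)² / 0.5² ≈ 62.8, so 63. The exact two-sample t test gives 63.77, so 64 per group, as stated.
- Carer share: (64 × 3)/0.79 = 243.04. With 10% loss: 243.04/0.90 ≈ 270, or 90 per group, as stated.
- Patients expected in the analysis: 90 × 0.90 = 81 per group.

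The sample size reproduces and is not affected by this point.

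**4. Illustration of scale only.** The documents give no figure for nurse-induced bias. The values of b below are assumptions, chosen as fractions of the 1.25-point target. SD 2.5 is assumed to apply to the change score.

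- Standard error of a pairwise difference: 2.5 × √(2/81) = 0.393.
- Probability of rejecting a true null when a spurious difference b is present: 1 − Φ(1.960 − b/0.393) + Φ(−1.960 − b/0.393).

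| Assumed b (points) | Share of 1.25 | b/0.393 | Rejection rate |
|---|---|---|---|
| 0.125 | 10% | 0.32 | 6.2% |
| 0.25 | 20% | 0.64 | 9.8% |
| 0.5 | 40% | 1.27 | 24.7% |
| 0.625 | 50% | 1.59 | 35.6% |

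The two-sample t test gives 9.7%, 24.4% and 35.3% for the last three rows. A shift of a tenth of the target would hardly matter, and one of two fifths would matter a great deal. The table does not say which of these, if any, is likely.

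**The case against.** Several points on the other side are sound.

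- **A reader might infer that the plan expects blinding to fail.** It does not. It says that blinding may be compromised, and it sets out measures to protect and check it.
- **A reader might infer that the carer outcome is clean by contrast.** It is not. Carers know the allocation, and their forms pass through the nurse for checking and data entry. Only the help step is absent.
- **A reader might infer that help is unnecessary because patients must be able to read and write English.** That criterion concerns literacy in English. The trial takes any stage of a movement disorder and a battery of about an hour, so some patients may well need help with writing. Help also serves the plan's aim of keeping missing data low.
- **A reader might infer that assistance is unrestricted and unrecorded.** The article does not say so. Order of forms, nurse scripts and record fields are commonly left to the full protocol, and silence in a condensed article is no evidence that they are absent.
- **The bias needs more than help.** The nurse must learn the arm and also influence answers differently by arm. Patients' own knowledge affects the scale whoever holds the pen.
- **The error rates rest on assumed shifts.** Any assumed bias raises the false-positive rate.

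What remains is a stated procedure. Help is the general rule for patients, it covers the primary outcome, and it comes from assessors whose blinding is acknowledged to be at risk. The existing check does not deal with this. A guess at the end of the trial can suggest that blinding was lost, but not when, nor which scores were affected.

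**Conclusion.** The point holds as a moderate, inexpensive improvement to a stated procedure. Nurse assistance with the self-assessed primary outcome, given by assessors who may have become unblinded, adds a detection-bias route to the one that comes from patients' own knowledge of their group.

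Its size cannot be derived from the documents. The rates of about 6% to 36% rest on assumed spurious differences of 0.125 to 0.625 points, 81 patients per group and an SD of 2.5 for change. They show only how sensitive one comparison would be.

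The documents do not support the stronger conclusion that an effect on disability would be uninterpretable, or that unaided completion would make the outcome free of bias. It would reduce the nurse-mediated part and leave the patient's own awareness in place.

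**What to change.** In Outcome measures, replace the general statement on assistance with a rule on these lines:

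1. At every visit the disability scale is completed first, before the other assessments and, at week 24, before any acceptability interview.
2. The patient completes it unaided where able.
3. Where help is needed, it is limited to reading items aloud or marking the patient's stated answer, without explanation or suggestion.
4. The same mode is kept across a patient's visits where possible.
5. Whether help was given, and of which kind, is recorded at each visit, baseline included.
6. Assistance is reported descriptively by arm and visit.

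Do not rely on an analysis restricted to unassisted completions. Need for help after randomisation is likely to be related to disability, the outcome itself. Such a subset could leave out the most impaired patients, and unequally by arm.

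If the full protocol or nurse manual already contains these rules, a sentence saying so is enough.

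**Cost.** A nurse instruction, a short record field and one descriptive table. Visits become slightly longer and a few more items may need a query, which the existing completeness check can pick up. Putting the scale before the interview protects the week 24 score. It does not protect week 36 if the interview reveals the arm to the same nurse.

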### Blinding

The research administrator will not disclose group allocation to the research nurses who undertake assessments, and participants will be asked not to discuss aspects of the trial and treatments with them. However, it is recognised that blinding of the research nurses may be compromised in trials of this nature. As a check on blinding, research nurses will be asked to guess participants' groups at the end of the trial. For data analysis, the group identifiers will not be disclosed to the statistician.

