### Registration and randomisation

After consent and baseline data have been collected, eligible volunteers will be given a unique registration number by the project administrator and randomised to either: Group A - specialist rehabilitation, Group B - specialist rehabilitation and ongoing care assistant support, or Group C - usual care, control group. A separate randomisation sequence will be prepared by the study statistician prior to the commencement of the study for patients without live-in carers and for patients with live-in carers. In each instance, blocked randomisation will be used to formulate the sequence involving the three comparison groups. A non-computerised random number generator will create random permuted blocks of size three with an equal allocation ratio (with any of the six different group sequences being equally possible). The project administrator will inform: all participants of the group to which they have been randomised; the MDT of participants randomised to either of the treatment arms; the GPs of all participants about their involvement in the trial and the group to which they have been randomised. Since the project administrator will not be involved in the process of consenting volunteers into the study, and randomisation of eligible participants will be conducted in chronological order of study entry, no attempt will be made to conceal from the project administrator the next group to which the next patient would be allocated. However, only the project administrator and the study statistician will have access to each randomisation sequence.

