### Statistical methods

Data will be entered into an SPSS (latest version) computer data-base using the registration number to identify the participant. All paper data will be stored in a secure locked cabinet, and all computer data will be stored on a secure server.

Baseline data will be analysed to describe the characteristics of the participants and to check for significant imbalance between the three groups. All outcomes will be analysed at each follow up assessment point (six, 24 and 36 weeks), and specific *a priori *hypotheses will be tested reflecting the outcomes that we expect to identify at the different stages. In each case a two sided test will be used. It is expected that t tests will be conducted to compare groups, unless any obvious deviations from t test assumptions are found in the outcomes, in which case the non - parametric Mann Whitney U test will be used.

In order to identify short term benefits, participants in the specialist rehabilitation groups (A and B) will be compared with participants receiving information pack only (group C) at six weeks. The null hypotheses will be tested, that there are no differences between the groups, with respect to change in patient disability, mobility and psychological wellbeing, and in carer strain. These hypotheses will be tested using each participant's change score from baseline (week 0) to week 6.

In order to identify medium term benefits, comparisons will be made at 24 weeks between pairs of treatment groups (Group A vs. Group B; Group A vs. Group C; Group B vs. Group C). The null hypotheses will be tested, that there are no differences between the groups with respect to change in patient disability, mobility, falls, speech, activities of daily living, social activities, psychological wellbeing, health related quality of life and use of health and social care services, and in carer strain, social activities and health related quality of life. These hypotheses will be tested using each participant's change score from baseline (week 0) to week 24.

In order to show loss or maintenance of benefit resulting from specialist rehabilitation, Group A (no ongoing support weeks 7 and 24) will be compared with Group B (ongoing support weeks 7 to 24) using the hypotheses in the medium term analysis and each participant's change score from week 6 to week 24.

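### The statistician is said to be blinded for analysis, yet the study statistician prepares and keeps access to the allocation lists; fixed blocks of three add avoidable predictability

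*Protocol article*

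**What the plan says.** All references are to the protocol article.

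- **Blinding:** "For data analysis, the group identifiers will not be disclosed to the statistician".
- **Registration and randomisation, who makes the lists:** "A separate randomisation sequence will be prepared by the study statistician prior to the commencement of the study for patients without live-in carers"; a second list covers patients with a live-in carer.
- **Same section, who can see them:** "only the project administrator and the study statistician will have access to each randomisation sequence".
- **Same section, structure:** "A non-computerised random number generator will create random permuted blocks of size three with an equal allocation ratio". All six orders of the three groups within a block are equally likely.
- **Same section, concealment:** "no attempt will be made to conceal from the project administrator the next group to which the next patient would be allocated". Two reasons are given: the administrator takes no part in obtaining consent, and people are randomised in the order in which they enter. Consent and baseline data come first.
- **Statistical methods:** the database identifies each participant by registration number. Groups are compared by t test, or by Mann-Whitney test if the data clearly violate the t test assumptions. At week 6 "participants in the specialist rehabilitation groups (A and B) will be compared with participants receiving information pack only (group C) at six weeks".
- **Management and governance:** the research team includes one statistician. The only other statistician mentioned sits on the external steering body.

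**The concern.** Two sections describe the same role in incompatible ways. Withholding a group variable from the analysis file does not blind someone who wrote the allocation list and can still consult it. A reader of the trial report would credit a safeguard that the design does not supply.

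The practical stake is the part of the analysis that depends on looking at the data. For every outcome and time point, the statistician decides whether the deviation from t test assumptions is marked enough to switch to the rank test. Blinding is what would protect that choice.

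A second and lesser point concerns the same lists. The block size is fixed at three in each stratum and stated openly, and the list is visible to the person who allocates. If information about earlier allocations escapes, later ones become easy to predict.

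**Working it through.** **1. Can the statistician link list to data?** Four facts are needed.

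- The list: held by the study statistician (Registration and randomisation).
- The stratum of each record: live-in carer or not, which follows from the caring arrangements recorded at baseline (Consent and baseline data collection).
- The order of allocation: the order of entry (Registration and randomisation).
- The order of the records in the database: available if registration numbers run in entry order. The protocol says only that the number is unique and is issued by the project administrator at this step, so this is an assumption.

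Given these, position in the stratum identifies the group for every record. Dummy labels alone would not prevent this. Each triplet contains every group once, so one triplet in known order shows which code stands for which group.

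**2. Do the planned comparisons unmask by themselves?** Only in part. The comparisons at weeks 24 and 36 cover all three pairs and are symmetric in the labels. The pooled A+B versus C test at week 6 and the A versus B test from week 6 to week 24 single out group C, but they do not separate A from B.

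**3. Predictability of a block of three.** The stated count of sequences reproduces: 3! = 6. For a guesser who knows the order, the block boundaries and all earlier allocations in the stratum:

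- first place: 1/3 correct; second: 1/2; third: 1
- average: (1/3 + 1/2 + 1)/3 = 11/18 = 61.1%, against 33.3% by chance
- certain allocations: 1 in 3, so 270/3 = 90 of the planned 270
- by stratum, using the protocol's 79% with a live-in carer: 270 × 0.79 ≈ 213, leaving 57; 213/3 = 71 and 57/3 = 19

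The administrator and the statistician hold the list, so for them every allocation is known.

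**4. What varying the block size would change.** The block of six is an illustration, not a figure from the protocol. With two places per group, always guessing the group with most places left, the success rates by place are 1/3, 2/5, 1/2, 8/15, 3/5 and 1.

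- Average: (101/30)/6 = 56.1%. Certain allocations: the sixth always and the fifth with probability 1/5, so 1.2/6 = 20.0%.
- Equal numbers of blocks of three and six, even if each block's size were known: (3 × 0.611 + 6 × 0.561)/9 = 57.8% correct and (1 + 1.2)/9 = 24.4% certain.

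If the sizes are not disclosed, the guesser usually cannot tell where a block ends, so these figures are upper limits.

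**The case against.** The strongest reply is that the open list is a disclosed and reasoned choice. Consent and baseline data precede randomisation, the research nurse rather than the administrator checks exclusions, the administrator does not take consent, and allocation follows order of entry. Nurses are not told allocations. The 61% belongs to a guesser whom the protocol does not create, because no recruiter or assessor is given the ordered list. The gain from larger blocks is modest when sizes are known. All of this stands, and it is why the block size and the open list are secondary.

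It can also be said that custody of codes is operational detail that an article may condense, and that nothing states that registration numbers follow entry order. The second part stands as an assumption. The first does not remove the conflict, because the article itself grants the statistician access in one section and asserts blinding in another.

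A reader might infer more than the document supports:

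- **That missing-data handling is left to an unblinded analyst.** The Missing data section fixes the main rules: exclusion at a time point where the outcome is missing, and multiple imputation in repeated measures analysis.
- **That one known allocation in a triplet reveals the other two.** In general it leaves an even guess. If the known one is a control, the other two are both treated, but not which is A and which is B.
- **That the comparisons cannot be run blind.** They can be programmed under dummy codes, although the pooled test marks out group C.
- **That referrals by Parkinson's nurses or therapists steer allocation.** Volunteers contact the research team themselves, and the treating team hears only of treatment-arm participants. Nothing shows that a referrer controls anyone's place in the sequence.

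**Conclusion.** The Blinding and the Registration and randomisation sections conflict, and blinding of the statistician is not a property of the design as written. This rests on two assumptions: that the study statistician is also the analyst, which the single statistician in the research team suggests, and that registration numbers follow entry order. The consequence is mainly for the choice between t test and Mann-Whitney test; no bias in a result can be computed from the document.

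The fixed triplets give 61.1% best-guess success against 33.3% by chance, with one third of allocations determined, to anyone who knows the order and the earlier allocations in a stratum. It would be going too far to conclude that allocation is compromised. That requires a leak or a departure from entry order, and the stated safeguards limit both. The Blinding section does concede that nurse blinding may fail, so the possibility is not empty. Sample size, power and significance level do not change. This should be corrected, but it does not undermine the trial.

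**What to change.** 1. Have someone who takes no part in the analysis generate and hold both lists, and withdraw the analysing statistician's access. If the lists have already been prepared, have a different person do the analysis.
2. Analyse under dummy group codes until the database is locked and the code is final. State that the pooled A+B versus C test will mark out group C.
3. Use randomly varying, undisclosed block sizes, for example 3 and 6, for allocations still to be made.
4. If list-holder and analyst cannot be separated, delete the claim that the statistician is blinded.

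The cost is a change of wording, custody of the lists by another person, and slightly looser running balance: within a stratum two groups can differ by at most one at any time with blocks of three, and by at most two with blocks of six. Who would take on custody is for the sponsor to settle. The external statistician is one possibility, but it would draw a member of the oversight body into running the trial.
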